### Statistical analysis

We plan to execute this trial in two stages, that is, we test the hypothesis in TKA first and then in THA, and the primary comparison will be performed separately for TKA and THA. An intent-to-treat analysis will be performed to analyze all primary and secondary outcomes by using SPSS18.0 software (Statistic Package for Social Science, SPSS, Inc., Chicago, IL, USA). The baseline continuous variables will be summarized using mean ± standard deviation or median (interquartile range) for continuous variables as appropriate. Categorical variables will be summarized using frequency (percentage).

Primary outcome: normality will be assessed for the primary outcome LOS. Appropriate transformation will be made if there is an assumption violation. We will use independent two-sample t-test to compare the LOS between the two groups. A *p* value < 5% will be considered as significant. For the primary outcome, we will also perform a sensitivity analysis using an analysis of covariance model (ANCOVA) with LOS as the response variable, the treatment group as the main factor adjusting for potentially imbalanced baseline characteristics and center effect.

For the primary outcome, we will also perform subgroup analysis based on subgroups defined by each of the age groups (< 65 years, ≥ 65 years), gender (male, female), and American Society of Anesthesiologists (ASA) class (I–II, III, or higher). Analyses will be performed for each subgroup in a similar way to the primary analysis.

For the secondary outcomes, the continuous variables (postoperative LOS, mobilization time, NRS, etc.) will be assessed for normality. Two-sample t-test or Wilcoxon rank sum test will be used for comparison depending on the normality test result. For categorical outcomes, odds ratio will be calculated and tested using Chi-square test. A *p* value < 0.05 will be considered statistically significant. We will use Kaplan–Meier plots to describe the mortality and compare the mortality at 30 days using a log rank test for fixed time points.

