### Sample size calculation

Our primary hypothesis is that the application of the ERAS pathway would reduce the LOS in hospital when compared to the current non-ERAS practice in total joint arthroplasty (TJA). According to retrospective analysis of LOS of in hospital of TJA in 2014 (when the ERAS pathway was just proposed) and 2016 (when the ERAS pathway was applied in about 50% of patients) in the Department of Orthopedics, West China Hospital of Sichuan University, the mean LOS of THA was 10 ± 1.5 days in 2014 and 8.6 ± 1.1 days in 2016; the mean LOS of TKA was 12.1 ± 2.1 days in 2014 and 8.9 ± 1.5 days in 2017. For THA, assuming the difference between the two groups was a 5% significance level and a power of 0.90, 17 patients in each group are required; for TKA, assuming the difference between two groups was a 5% significance level and a power of 0.90, only seven patients in each group are required for a comparison within the group. Considering an estimated 20% dropout rate, there should be 42 patients in each group for THA and 20 patients in each group for TKA; a total of 62 patients are required for this study [10]. For a better application of the ERAS pathway for orthopedic surgeons and anesthesiologists, we increased the sample size to 160 individuals in each group for THA and TKA, and a total of 640 individuals will be included. We plan to enroll 320 patients undergoing TKA to participate in this trial in the first stage and enroll 320 patients undergoing THA after completion. A primary comparison will be performed separately for TKA and THA.

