### Outcome measures

#### Primary outcome

The primary outcome is LOS in hospital, which is defined as the time frame from the day of hospital admission to discharge from the hospital (unit: days).

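### A normality check on the trial data decides the scale of the primary LOS comparison and the test for each continuous secondary outcome, so what is estimated is not fixed in advance

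*Protocol article*

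**What the plan says.** All of this is in the protocol article.

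- **Outcome.** The Primary outcome section defines LOS as "the time frame from the day of hospital admission to discharge from the hospital (unit: days").
- **Primary analysis.** Under Statistical analysis, "normality will be assessed for the primary outcome LOS". Then: "Appropriate transformation will be made if there is an assumption violation". Then: "We will use independent two-sample t-test to compare the LOS between the two groups". The rule for leaving the day scale depends on the data, and the scale to move to is not named.
- **Sensitivity analysis.** This is a "sensitivity analysis using an analysis of covariance model (ANCOVA) with LOS as the response variable". The text does not say whether LOS is transformed there too.
- **Secondary outcomes.** "the continuous variables (postoperative LOS, mobilization time, NRS, etc.) will be assessed for normality", and "Two-sample t-test or Wilcoxon rank sum test will be used for comparison depending on the normality test result". Total in-hospital cost is a listed secondary outcome and is continuous, so the open-ended list covers it by implication.
- **Planning basis.** The Sample size calculation works in mean days, for example "the mean LOS of THA was 10 ± 1.5 days in 2014 and 8.6 ± 1.1 days in 2016". The Discussion justifies LOS by medical cost and resource use, and hypothesises no increase in cost.

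**The concern.** The trial is planned to detect a difference in mean days. If the check leads to a log scale, the t-test compares geometric means. If it leads to Wilcoxon, the comparison is of ranks. Both give less weight to a few long, expensive stays, and those stays drive bed use and cost. The conclusion could then answer a different question from the one planned.

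TKA is tested first and THA afterwards, each separately, so the two joints could end up on different scales. So could the primary t-test and its ANCOVA sensitivity analysis.

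The check may also respond to the wrong feature. With SDs of 1.1 to 2.1 days, LOS in whole days takes few distinct values. A formal test at 160 per arm can reject because of that rounding, which does little harm to a t-test.

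**Working it through.** **1. The plan's own figure.** Inputs from Sample size calculation: THA 10 (SD 1.5) v 8.6 (SD 1.1); TKA 12.1 (SD 2.1) v 8.9 (SD 1.5); 5% significance level; power 0.90. Two-sided testing is assumed.

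n per group = 2(1.960 + 1.282)² × s²/d², with s² the mean of the two variances.

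- THA: s² = (2.25 + 1.21)/2 = 1.73, d = 1.4. n = 2 × 10.51 × 1.73/1.96 = 18.6, so 19 (stated: 17; one-sided gives 16).
- TKA: s² = (4.41 + 2.25)/2 = 3.33, d = 3.2. n = 2 × 10.51 × 3.33/10.24 = 6.8, so 7 (stated: 7).

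The stated sizes are matched exactly for TKA and within 2 for THA, which confirms that the plan rests on mean days on the raw scale.

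**2. How often would a formal test reject?** Each arm was simulated 1,000 times with the four planning means and SDs and tested at 5%.

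| LOS as recorded | Underlying shape | Rejection |
|---|---|---|
| Whole days, n = 160 | normal, gamma, lognormal, or skewness 1 | 100% (Shapiro-Wilk and Lilliefors) |
| Log of whole days, n = 160 | same | 100% |
| Whole days, n = 128 (160 × 0.8) | same | 97–100% |
| Unrounded, n = 160, Shapiro-Wilk | normal | 4–6% |
| Unrounded, n = 160, Shapiro-Wilk | gamma | 22–35% |
| Unrounded, n = 160, Shapiro-Wilk | lognormal | 38–64% |
| Unrounded, n = 160, Shapiro-Wilk | skewness 1 | over 99% |

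Only the log transformation was simulated, but any one-to-one transformation keeps the ties.

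**3. What changes with the scale.** Raw: −1.4 days (THA) and −3.2 days (TKA). On the log scale, if LOS is lognormal, the geometric mean is m/√(1 + (s/m)²). THA: 8.53/9.89 = 0.86. TKA: 8.78/11.92 = 0.74. Wilcoxon gives a rank-based quantity.

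**4. Can the answers diverge?** An assumed example, not taken from the documents: the typical stay is 0.5 day shorter with ERAS, but 7% v 3% of stays are prolonged by 12 days. Mean difference = −0.5 + 12 × (0.07 − 0.03) = −0.02 day. Rejection at 160 per arm, over the four planning mean/SD pairs:

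- raw t-test: about 4–6%
- log t-test: 8–16% (relevant to the primary outcome)
- Wilcoxon: 22–83% (relevant to secondary outcomes only)

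The higher rates are not errors of those tests. They detect a real shift in the typical stay, which is not a shift in mean days.

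**5. Type I error.** With identical skewed whole-day distributions in both arms (20,000 runs, 160 per arm), each test alone held 4.7–5.0%. Always taking the smallest p-value among raw, log and reciprocal t-tests gave 5.8–7.9%; between t-test and Wilcoxon, 6.0–6.7%.

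**6. Price of staying on days.** The raw t-test's type I error in step 5 was 4.8–4.9%. Power for the planned differences is over 99.9% at 160 and at 128 per arm. With the heavier tail of step 4 and base SD 1.5, the variances are 2.25 + 144 × 0.03 × 0.97 = 6.44 and 2.25 + 144 × 0.07 × 0.93 = 11.62. For a THA difference of 1.4 days, 1.4/√(18.06/160) = 4.17, so power is about 99%. At 128 per arm, 1.4/√(18.06/128) = 3.73, about 96%.

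**The case against.** Several objections stand and limit the point.

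- A reader might infer that the primary rule will almost always trigger a transformation. The text does not establish that. For the primary outcome normality is only to be assessed; a test is mentioned only for secondary outcomes. Simulated normal LOS rounded to days had a mean absolute skewness of about 0.15, which a plot would probably pass. Whole-day recording is itself inferred from the unit; with half-day rounding, rejection ranged from 20% to 100%.
- A reader might apply the Wilcoxon figures to the primary outcome. That would be wrong: a t-test is fixed there, raw or transformed. The figures also come from simulated stays, so they carry over to cost only by analogy.
- The example is deliberately adverse. Its SDs, √6.44 = 2.5 and √11.62 = 3.4 days, exceed the planning range of 1.1–2.1, and ERAS must more than double prolonged stays while shortening typical ones. It shows that divergence is possible, not that it is likely.
- A reader might suspect serious inflation of false positives. Step 5 shows it is modest even with free picking, and Randomization and blinding says the statisticians are blinded.
- A condensed article may leave the named transformation and effect measure to a SAP. True, and their absence is not the point. The point is the stated rule, which a SAP that followed it would inherit.

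**Conclusion.** The point holds in limited form, and the plan should be changed. The article states a data-dependent rule for the scale of the primary comparison and for each continuous secondary test, while its sample size rests on mean days and its hypothesis extends to cost. The damage is to the estimand and its interpretation, much less to error rates (about 6–8% at worst) and not to power.

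Rejection in about 100% of arms depends on two assumptions: whole-day recording and a formal test. Without rounding, it ranges from about 4% to over 99% according to skewness. It was computed for LOS and not for cost, pain scores or mobilization time. The case for change does not need that figure: the raw-scale t-test already performs well at this sample size, so the check has little to offer whichever way it comes out.

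**What to change.** Remove the normality check as a decision rule and state in advance:

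- **Primary:** difference in mean LOS in untransformed days, by unequal-variance (Welch) t-test with a 95% CI, the same for TKA and THA. The planning SDs differ between groups, which is why the unequal-variance form is suggested.
- **ANCOVA sensitivity analysis:** keep it, on untransformed days.
- **Cost:** difference in mean cost with a bootstrap CI.
- **Other continuous secondary outcomes:** one named test each.
- **Transformed or rank-based analyses:** sensitivity only.

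A different primary model, such as a centre-adjusted one with robust standard errors, is not needed to cure this defect.

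The cost is wording. Some power is lost if a few stays are very long, but little: step 6 still gives about 96–99% for the smaller planned difference under the heavy-tailed example, and over 99.9% at the planning SDs.

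### Subgroup effects on LOS are to be tested stratum by stratum with no interaction test, so a significant result in one stratum and not in the other may be misread as a difference in effect

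*Protocol article*

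**What the plan says.** Everything on this point stands in the protocol article.

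- **Factors.** Under Statistical analysis, the LOS subgroups are "subgroups defined by each of the age groups (< 65 years, ≥ 65 years), gender (male, female), and American Society of Anesthesiologists (ASA) class", with ASA split at class III.
- **Method.** The next sentence reads "Analyses will be performed for each subgroup in a similar way to the primary analysis".
- **What the primary analysis is.** "We will use independent two-sample t-test to compare the LOS between the two groups", with a p value below 5% that "will be considered as significant".
- **Procedures.** "the primary comparison will be performed separately for TKA and THA". Under Sample size calculation, each procedure has 160 patients per arm: "we increased the sample size to 160 individuals in each group for THA and TKA".
- **The only model for LOS.** A sensitivity ANCOVA with "the treatment group as the main factor adjusting for potentially imbalanced baseline characteristics and center effect". No treatment-by-subgroup term is described.

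The article mentions no test of interaction or heterogeneity, and it does not call the subgroup results exploratory.

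**The concern.** A subgroup analysis asks whether the treatment effect differs between, say, patients under 65 and those 65 or older. A t-test within each stratum asks something else, namely whether the effect in that stratum differs from zero. Two such p values can fall on opposite sides of 0.05 although the effect is identical, simply because one stratum is smaller or by chance. They can also both be significant although the effects differ. The stated method therefore cannot answer the question for which subgroups are examined.

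What is at stake is the subgroup conclusions, not the primary one. A report that ERAS shortened stay in ASA I–II but not in ASA III or higher could rest on noise.

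**Working it through.** **Number of tests.** Three factors with two levels each give 6 strata per procedure, and 6 × 2 procedures = 12 tests. This rests on two readings: that ASA has two levels (the punctuation of the list leaves some doubt), and that subgroup analyses, like the primary comparison, are done separately for TKA and THA.

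**Inputs from Sample size calculation.**
- THA: 10 ± 1.5 against 8.6 ± 1.1 days. Difference 1.4; SD = √((1.5² + 1.1²)/2) = 1.315.
- TKA: 12.1 ± 2.1 against 8.9 ± 1.5 days. Difference 3.2; SD = √((2.1² + 1.5²)/2) = 1.825.
- 160 per arm per procedure, with no loss.

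As a check on these inputs, n per arm = 2(1.96 + 1.2816)² SD²/δ² gives 19 for THA (article: 17) and 7 for TKA (article: 7). This point does not contest those figures.

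**Assumed.** Two-sided tests (not stated), the stratum shares (none are given), equal allocation within strata, and the same true effect in both strata.

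**Formulas.** For a stratum with n patients per arm, ncp = δ/(SD√(2/n)) and power = Φ(ncp − 1.96) + Φ(−ncp − 1.96). With powers a and b in the two strata, the chance that exactly one is significant is a(1 − b) + b(1 − a).

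**Example: THA, planned effect, 80/20.** The strata have 128 and 32 per arm.
- Large: 1.4/(1.315 × √(2/128)) = 8.52, power 1.000.
- Small: 1.4/(1.315 × √(2/32)) = 4.26, power 0.989.
- Split result: 1 × 0.011 + 0.989 × 0 = 1.1%.

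**Example: half that effect (0.7 day), 80/20.**
- ncp 4.26 and 2.13, power 0.989 and 0.567.
- Split result: 0.989 × 0.433 + 0.567 × 0.011 = 43%. With the noncentral t distribution it is 45%.

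**Chance of a split result for one factor when the effect is the same in both strata:**

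| True effect, SD | 50/50 | 80/20 | 90/10 | 95/5 |
|---|---|---|---|---|
| TKA planned: 3.2 days, 1.825 | 0% | 0% | 0.1% | 6% |
| THA planned: 1.4 days, 1.315 | 0% | 1.1% | 15% | 43% |
| Half THA: 0.7 day, 1.315 | 15% | 43% | 67% | 81% |
| 0.55 day, 1.5 | 46% | 63% | 74% | 80% |

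The table uses the normal formula. The noncentral t gives slightly more, for example 17% for planned THA at 90/10. At 95/5 the small stratum has only 8 per arm and the normal figures are low: power for THA (ncp 2.13, 14 df) falls from 0.57 to 0.51, so the split chance is nearer 49%; for TKA it is nearer 10%.

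The last row is a constructed case. It is roughly the effect for which 160 per arm has 90% power at SD 1.5: ncp = 0.55/(1.5 × √(2/160)) = 3.28.

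**No effect at all.** Six independent tests would give 1 − 0.95⁶ = 26.5%. The six strata overlap, so the true figure is lower: simulated trials with assumed shares of 50%, 65–70% and 80% give 20–21% per procedure. Over both procedures that is about 1 − 0.80² = 36%.

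**Under the replacement.** Three interaction tests per procedure give 1 − 0.95³ = 14.3% (14–15% in simulation).

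**The case against.** **At the planned effects the problem hardly shows.** For balanced strata, and even at 80/20, both strata would almost always be significant. This stands, and a reader who took the 46% or 63% of the constructed 0.55-day case as the expected risk would overstate it. That effect is 39% of the planned THA difference (0.55/1.4) and 17% of the TKA one (0.55/3.2). The article says the sample was raised to 160 per arm for better application of the pathway, not to detect such an effect. Nor may one infer that ASA III or higher will usually be non-significant: at the planned effects that fails for a 20% stratum. Still, the planned differences come from retrospective comparisons between years at one hospital. The trial randomises at eight hospitals against unrestricted usual care, and in both arms the responsible physician decides on catheter, drain and tourniquet. A smaller effect is plausible, and small strata are exposed even at the planned THA effect.

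**The article does not say how the results will be read.** True. It states no subgroup hypothesis and no rule for comparing strata. That differences in significance *will* be reported as differences in effect is a forecast the document does not support; they *may* be.

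**Such detail belongs in the SAP.** Forest plots and exploratory labels often do, and an unseen SAP could add an interaction test. But the article is not silent: it fixes a method, and that method does not compare strata.

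**The remedy also produces false positives.** It does, in about 14% of trials per procedure against about 20%. The main gain is that the test addresses the right question, not the lower error rate.

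In the plan's favour, the three factors and the age and ASA cut-points are named in advance and confined to the primary outcome.

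**Conclusion.** The point holds for the method: stratum-by-stratum t-tests do not assess whether the effect of ERAS on LOS differs by age, gender or ASA class, and nothing in the article supplies a test that does. This is true whatever the effect size.

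The practical risk is conditional. It is small for THA and negligible for TKA at the planned differences, unless a stratum holds about 10% of patients or fewer (THA) or about 5% (TKA). It is large if the true effect is half the THA figure or less and a stratum is small. These sizes rest on assumed shares, two-sided tests, a common effect and full enrolment. With the 20% dropout that the article allows for, strata would be smaller and the figures somewhat higher. The primary comparison is not affected, so the change is advisable rather than essential.

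**What to change.** Replace the sentence on subgroup method with wording such as: *For each procedure separately, each subgroup factor will be assessed by a treatment-by-factor interaction term in a linear model of LOS containing treatment, the factor and centre. The difference in effect between strata will be reported with its 95% confidence interval. Stratum-specific effects will be shown with 95% confidence intervals and without p values. All subgroup results are exploratory.* State also that ASA has two levels, if that is meant.

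The planned sensitivity ANCOVA, which already includes centre, can carry the term. The primary analysis stays the unadjusted t-test.

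The cost is wording only, with no new data or patients. The downside is low power. For THA the overall standard error is 1.315 × √(2/160) = 0.147 day. The interaction multiplies it by √(1/0.5 + 1/0.5) = 2 at 50/50 and √(1/0.8 + 1/0.2) = 2.5 at 80/20. With 80% power, the smallest detectable difference in effect is then 2.80 × 0.294 = 0.82 day and 2.80 × 0.368 = 1.03 days. A non-significant interaction therefore does not show equal effects. As three unadjusted tests also leave about a 14% chance of a false positive per procedure, the exploratory label is needed.

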#### Secondary outcomes

i.Postoperative LOS, which is defined as the time frame from the day of operation to discharge from the hospital (unit: days).ii.All-cause mortality by 30 days after operation.iii.In-hospital complications, which are divided into five grades:
Grade I: recovery after temporary treatment, e.g. postoperative nausea and vomiting (PONV), postoperative anxiety, insomnia.Grade II: prolonged hospitalization, e.g. pulmonary infection requiring antibiotics or other treatment, surgical wound infection requiring wound debridement.Grade III: life-threatening complications requiring intense treatment during hospitalization and resulting in good functional recovery, e.g. dialysis therapy for acute renal insufficiency, mechanical ventilatory support for respiratory failure, or postoperative bleeding requiring re-operation.Grade IV: life-threatening complications resulting in significantly decreased quality of life, e.g. myocardial infarction, stroke that left paralytic limbs.Grade V: all-cause mortality by 30 days after operation, which is defined as a secondary outcome.iv.Mobilization time, which is defined as the time frame from the end of operation to the ability to walk without external assistance (unit: hours).v.Numerical rating scales (NRS) scores at rest during three days after operation.vi.NRS scores during mobilization or physical therapy during three days after operation.vii.Postoperative sufentanil or other analgesics requirement during three days after operation.viii.Total in-hospital cost.ix.Readmission rate by 30 days after discharge from the hospital.

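### The NRS pain scores, repeated over three days, are given a test that takes one value per patient; the plan does not say which value, and the test omits centre, the randomization stratifier

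*Protocol article*

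**What the plan says.** The Secondary outcomes section of the protocol article defines two pain outcomes: "Numerical rating scales (NRS) scores at rest during three days after operation" and "NRS scores during mobilization or physical therapy during three days after operation". It states neither the number of readings per day nor a per-patient summary such as a mean or worst score.

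The Statistical analysis section groups NRS with postoperative length of stay and mobilization time: "the continuous variables (postoperative LOS, mobilization time, NRS, etc.) will be assessed for normality". The method follows: "Two-sample t-test or Wilcoxon rank sum test will be used for comparison depending on the normality test result". The threshold is a p "value < 0.05 will be considered statistically significant". For NRS, no repeated-measures model, main time point or multiplicity rule is named.

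The Randomization and blinding section stratifies allocation by the eight hospitals. Centre enters the analysis only in the ANCOVA, which is a sensitivity analysis of the primary outcome.

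**The concern.** Postoperative length of stay and mobilization time give one number per patient, so a two-sample test fits them directly. NRS over three days gives several correlated numbers per patient, so the same test fits only after they are reduced to one. The plan names the test but not the reduction. Three readings of the text remain open:

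- one test on a per-patient summary;
- a separate test for each day;
- one test on all readings pooled.

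These readings have different error rates and different precision. Under daily testing, the normality rule could also select a t-test on one day and a rank test on the next, so the daily results would not be comparable.

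Pain matters in this comparison. The ERAS pathway excludes patient-controlled intravenous analgesia devices after surgery, whereas analgesia in the control arm is unrestricted. The Discussion itself anticipates rapid onset of pain once remifentanil stops. An isolated significant day, or a real difference missed because days were tested singly, would cloud the account of pain control. Control care also follows local practice, so pain scores may differ between hospitals, and the named tests make no allowance for that.

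**Working it through.** **Inputs from the protocol.** Two pain outcomes, each over three days (Secondary outcomes). Level 0.05 per test (Statistical analysis). Size: "we increased the sample size to 160 individuals in each group for THA and TKA, and a total of 640 individuals will be included", hence 160 per arm per joint. Dropout 20%, leaving 160 × 0.8 = 128 per arm. The protocol gives no sample size, power or error rate for NRS, so it has no figure of its own to reproduce here.

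**Assumptions.** Two-sided tests; one reading per day and condition; equal within-patient correlation ρ of 0.3, 0.5 or 0.7 (not in the documents); no missing scores; NRS analysed separately by joint. That separation is stated only for the main outcome: "A primary comparison will be performed separately for TKA and THA".

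**1. Chance of at least one false positive, unadjusted daily tests.** If independent: 1 − 0.95³ = 0.143 for three tests and 1 − 0.95⁶ = 0.265 for six. With correlated statistics (simulated null z-statistics, 1,000,000 draws, all pairs correlated at ρ):

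| ρ | 3 days, one outcome | 6 tests, rest and movement |
|---|---|---|
| 0.3 | 0.136 | 0.241 |
| 0.5 | 0.126 | 0.207 |
| 0.7 | 0.109 | 0.164 |

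**2. The like-for-like comparator.** One overall test per outcome still means two tests. If independent: 1 − 0.95² = 0.0975. If the two statistics are correlated at 0.5: about 0.09. So the six-test figures should be set against about 9%, and the three-test figures against 5%.

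**3. Readings pooled as if independent.** The true variance is 1 + 2ρ times the assumed one, so the type I error is 2[1 − Φ(1.96/√(1 + 2ρ))]. This gives 0.121, 0.166 and 0.206 at ρ = 0.3, 0.5 and 0.7.

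**4. One test on a per-patient three-day mean.** Each patient contributes one value, so the type I error is 0.05 per outcome.

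**5. Precision.** The detectable difference at 90% power is (1.960 + 1.282) × √(2/n) SD for one day. For the three-day mean, multiply by √((1 + 2ρ)/3), since its variance is 0.533, 0.667 or 0.800 of a single day's.

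| | n = 160 per arm | n = 128 per arm |
|---|---|---|
| One day | 0.362 SD | 0.405 SD |
| Three-day mean, ρ = 0.3 | 0.265 SD | 0.296 SD |
| Three-day mean, ρ = 0.5 | 0.296 SD | 0.331 SD |
| Three-day mean, ρ = 0.7 | 0.324 SD | 0.362 SD |

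The SD is that of a single day's score. With complete data, the average arm difference from a mixed model with a patient random effect has the same precision as the three-day mean.

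**6. Centre.** An unadjusted test after stratified allocation keeps the between-hospital variation in its error term. The documents give no NRS variance by hospital, so the loss cannot be sized.

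**The case against.** A reader might infer that the plan ignores the repeated measures and therefore loses precision and inflates false positives. The documents do not support that. They say neither that tests are run day by day nor that readings are pooled. Each pain outcome is worded as one item covering three days, which is compatible with one summary per patient and one test. The analgesic requirement over the same three days reads naturally as a total. A two-sample test on a per-patient mean is a valid analysis of repeated scores: it holds 5%, and with complete data it matches a mixed model for precision. This objection stands in full, so both harms are conditional.

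It is also fair that the choice of summary is often left to an analysis plan, and that the sentence covers a class of variables and ends in an open list. This stands in part. Such a plan may fix the value, and its absence here is not the point. But the protocol does commit to a method for NRS by name. That method is shared with outcomes that yield a single number, and it leaves out the factor by which randomization was stratified.

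Finally, a mixed model is not the only sound remedy, and pain accounts for two of nine secondary outcomes. Both points stand.

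**Conclusion.** The point holds as an inexpensive improvement to two secondary outcomes, not as an error that certainly distorts them. The stated test needs one value per patient, the value is not stated, and centre is omitted.

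If the tests are run daily without adjustment, the chance of a false positive is about 11-14% over three days, against 5% for one test. Over six tests it is 16-24%, against about 9% for two overall tests correlated at 0.5. A single day then detects 0.362 SD, where the three-day average detects 0.265 to 0.324 SD. Pooling readings as independent would give a type I error of 12-21%. A prespecified three-day mean has none of these problems.

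All ranges rest on the assumed correlations of 0.3 to 0.7 and one complete reading per day and condition. The primary length-of-stay conclusion does not depend on any of this.

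**What to change.** In the Statistical analysis section, take NRS out of the general sentence on continuous outcomes and give each of the two pain outcomes one prespecified analysis:

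- a linear mixed model with arm, day, arm-by-day and centre, and patient as a random effect, whose single test is the average arm difference over the three days; or
- equivalently with complete data, a centre-adjusted comparison of the per-patient three-day mean, with a stated rule for patients who miss a day.

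Report the daily arm differences with confidence intervals as description only, without daily significance claims.

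The cost is a few sentences of analysis text. No additional data are needed, because the scores are already planned. The second option uses the kind of covariance model already planned for length of stay. The change should be made before any comparison by arm.

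### The log-rank test named for 30-day mortality is not a comparison at a fixed time point, and it gives no estimate or interval for the 30-day risk difference

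*Protocol article*

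**What the plan says.** Item ii under Secondary outcomes is "All-cause mortality by 30 days after operation". The same event appears again as the top complication grade: "Grade V: all-cause mortality by 30 days after operation, which is defined as a secondary outcome".

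The last paragraph of Statistical analysis gives mortality its own sentence. Kaplan-Meier plots will describe it, and the trial will "compare the mortality at 30 days using a log rank test for fixed time points". The general rule for yes/no outcomes comes earlier in that paragraph: "For categorical outcomes, odds ratio will be calculated and tested using Chi-square test". The threshold for secondary outcomes is that a p "value < 0.05 will be considered statistically significant".

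On size, the protocol states that "we increased the sample size to 160 individuals in each group for THA and TKA". It also states that "the primary comparison will be performed separately for TKA and THA"; whether mortality is split by joint in the same way is not said. No mortality rate, expected number of deaths or power for mortality is given. The Discussion names 30-day mortality among the secondary outcomes that bear on the trial's hypothesis.

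**The concern.** The sentence on mortality joins two different analyses. A comparison at day 30 asks whether the proportion dead by that day differs between arms. A log-rank test adds up observed minus expected deaths at every death time and asks whether the two curves differ over the whole period. It has no version for a fixed time point, so an analyst could carry out the sentence as a curve comparison or as a day-30 comparison.

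The more practical issue is what gets reported. The log-rank statistic comes with a p-value and nothing on the scale of the outcome. The trial wants to say that a shorter stay does not come at the price of harm. With few deaths, a large p-value is almost certain and says little. The useful information is how large an increase in 30-day mortality remains compatible with the data, and only an estimate with an interval shows that.

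**Working it through.** The protocol has no mortality figure to reproduce; its sample size calculation concerns length of stay only. The checks below use N = 160 per arm (Sample size calculation). They assume complete follow-up to day 30 and two-sided tests at 0.05.

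**1. Does the mismatch change the p-value?** With a and b deaths in two arms of N, the uncorrected chi-square statistic is X² = 2N(a − b)² / [(a + b)(2N − a − b)].

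- 0 v 4: 320 × 16 / (4 × 316) = 4.051, p = 0.044.
- 0 v 5: 320 × 25 / (5 × 315) = 5.079, p = 0.024.
- 1 v 3: 320 × 4 / (4 × 316) = 1.013, p = 0.314.

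The log-rank statistic for 0 v 4, with deaths at distinct times:

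- Expected deaths in the arm with the deaths: 160/320 + 159/319 + 158/318 + 157/317 = 1.991.
- Variance: the sum of e(1 − e) over these four terms = 1.000.
- Statistic: (4 − 1.991)² / 1.000 = 4.04, p = 0.044.

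For 0 v 5 the log-rank p is 0.024. For 1 v 3 it lies between 0.313 and 0.317, depending on when the deaths occur. Timing hardly matters when deaths are rare: 8 early deaths in one arm against 8 late deaths in the other gives p = 0.96.

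**2. Is the large-sample test too liberal with sparse deaths?** Give both arms the same true risk. The false-positive rate is the sum of Bin(a; 160, risk) × Bin(b; 160, risk) over all pairs (a, b) with p < 0.05. The risks are assumptions.

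| Assumed 30-day mortality | Expected deaths (320 × risk) | Chi-square | Fisher |
|---|---|---|---|
| 0.1% | 0.3 | 0.004% | below 0.001% |
| 0.3% | 1.0 | 0.2% | 0.001% |
| 0.5% | 1.6 | 0.8% | 0.016% |
| 1% | 3.2 | 3.2% | 0.25% |
| 2% | 6.4 | 4.5% | 1.3% |

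The chi-square test, and so the log-rank test that tracks it, stays below 5% throughout. Fisher's test is more conservative still.

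**3. What does an interval add?**

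- With 0 deaths in N, the exact two-sided 95% upper limit for that arm's risk is 1 − 0.025^(1/N). For N = 160 it is 2.28%; for N = 320 (both joints pooled) it is 1.15%. These limits are for one arm's risk, not for the difference.
- For the difference, take 1/160 in control and 3/160 under ERAS. The log-rank p is about 0.31. Wilson 95% limits are 0.11% to 3.45% for 1/160 and 0.64% to 5.37% for 3/160. The score-based (Newcombe) interval around 1.875 − 0.625 = 1.25 percentage points is:
  - lower limit: 1.25 − √[(1.875 − 0.64)² + (3.45 − 0.625)²] = −1.8 points;
  - upper limit: 1.25 + √[(5.37 − 1.875)² + (0.625 − 0.11)²] = +4.8 points.

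The p-value alone reads as no difference. The interval shows that an increase of nearly five percentage points is not excluded.

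**The case against.** The strongest reply is that this is loose wording with no inferential consequence. With follow-up ending at day 30, the log-rank test compares mortality through day 30, and step 1 shows that its p-value practically equals that of a two-proportion test. That stands. It is also fair that low information on a rare secondary outcome is not an error, that the trial is powered on length of stay only, and that no equivalence claim for mortality is made. Interval methods and sparse-data rules are often left to an analysis plan. What remains is that the protocol did name a method here, and the method does not do what the sentence says.

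Three stronger readings are tempting, and the documents do not support them.

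- **That a planned odds ratio for mortality will fail.** If the risk is p in both arms, the chance that at least one arm has no deaths is 1 − [1 − (1 − p)^160]². That is 98% at 0.1% mortality, 70% at 0.5%, 36% at 1% and 8% at 2%. But the odds-ratio rule is not assigned to mortality, which has its own sentence, and the Grade V entry points back to mortality as a separate outcome.
- **That deaths will be too few for any usable result.** No mortality rate is given, and the figures above change greatly across a plausible range.
- **That the large-sample test would produce false significance.** The 0 v 4 split (chi-square p = 0.044, Fisher p = 0.12) suggests this, but step 2 shows that the test is already conservative. Fisher's test would make a non-significant result more likely still.

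**Conclusion.** The point holds in a limited form. The stated test does not perform the stated fixed-time comparison, and it supplies no estimate or interval for the 30-day risk difference. The cost lies in what can be reported about an outcome tied to the hypothesis, not in the validity of the p-value.

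The size is small. It concerns one secondary outcome, leaves the length-of-stay analysis untouched, and would rarely change a significance call. The near-equality of the two p-values assumes near-complete follow-up to day 30. The sample size section allows for 20% dropout without saying whether that applies to vital status. The 2.3% limit assumes 160 per arm and no deaths in that arm; it is an illustration, not a forecast.

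**What to change.** Replace the mortality sentence with: deaths by day 30 are reported as number and proportion per arm, with the risk difference and an exact or score 95% confidence interval as the main mortality result; Kaplan-Meier curves are descriptive. If the log-rank test is kept, delete its closing words about fixed time points and say that it compares the curves from day 0 to day 30. An exact test is optional. It would help to state whether mortality is reported by joint, pooled or both, and what denominator is used when day-30 status is unknown.

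The cost is one changed sentence, with no change to data collection or sample size. The downside is an interval that will probably be wide, but that width is the honest summary of what the trial can say about mortality.
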